## 2. Materials and Methods

Design: We proposed a randomized, double-blind, sham-controlled clinical trial to test the effects of the accelerated iTBS protocol in participants with schizophrenia with negative symptoms (CONSORT—Figure 1). The study is conducted in accordance with the Declaration of Helsinki and has been approved by the Research Ethics Committee of the Federal University of São Paulo (UNIFESP) as of 14 September 2023 and registered in The Brazilian Registry of Clinical Trials (ReBEC) (CAEE: 71102823.4.0000.5505).

*Participants*:

We will recruit 60 volunteers, aged between 18 and 50 years of both genders, who have been diagnosed with schizophrenia according to the criteria of the Diagnostic and Statistical Manual of Mental Disorders (DSM-5), through an evaluation conducted via the Structured Clinical Interview for DSM-5 (SCID-5) and who present negative symptoms of moderate intensity (score ≥ 20 on the BNSS). Participants must have stable medication use, with no changes in antipsychotics in the three months prior to inclusion, and must not be using medications that could lower the seizure threshold, except for antipsychotics. Additionally, participants should not have a history of substance dependence or alcohol use in the past four weeks. In the case of smokers, the number of cigarettes and the last use will be documented. Regarding neuromodulation, participants should not have undergone any brain stimulation protocols in the past year prior to study enrollment. All participants must sign the informed consent form to participate in the study.

Participants will be allocated into two groups (intervention and sham), with 30 subjects per group. The statistical power for the primary analysis with this sample size is estimated to be β = 0.82. This calculation assumes (1) the use of mixed linear regression models for hypothesis testing, which will assess the interaction between time (baseline vs. T1) and treatment (intervention vs. sham), (2) a moderate effect size (f = 0.38), and (3) a significance level of 5% (two-tailed).

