### 2.3. Heart Rate Variability

Data collection of the electrocardiogram (ECG) will be conducted using the Neuro-EMG Micro equipment and PolySpectrum software (Neurosoft, Russia, version 5.3.1.0 released 15 November 2017, with a sampling frequency of 1000 Hz and a 60 Hz notch filter. The patient will remain seated and motionless in a comfortable chair to allow for acclimatization and autonomic stabilization. During this period, the electrodes (RA, LA, LL) will be placed, and signal quality will be continuously monitored. After stabilization, a 5 min baseline will be collected. Subsequently, an additional 7 min of data will be recorded for heart rate variability (HRV) analysis.

The analysis will be performed using Kubios HRV Scientific software (ver. 4.1, Win & Mac, October 2023), calculating measures in the time domain (SDNN, RMSSD, and pNN50), in the frequency domain (VLF, LF, HF, and LF/HF ratio), and sample entropy (SampEn). The factory default settings will be used, including automatic artifact correction at a medium level, automatic beat correction, an interpolation rate of 4 Hz, and a trend removal method. All collections and analyses will adhere to the guidelines set forth by the Task Force of the European Society of Cardiology and the North American Society of Pacing and Electrophysiology (1996).

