### 2.5. Statistical Analysis

The effects of the intervention will be analyzed according to the intention-to-treat (ITT) paradigm, which assesses the effect on all participants, regardless of their level of adherence to the treatment. The primary outcome of the study will be the reduction of negative symptoms, measured by the total score of the Brief Negative Symptom Scale (BNSS) with a score ≥20, while the secondary outcomes will focus on the reduction of negative symptoms as assessed by the negative symptom subscale score of the Positive and Negative Syndrome Scale (PANSS), the sub-domains of BNSS and physiological variables, through HRV assessment, sleep alterations and their association with negative symptoms, assessed by Pittsburgh and Epworth scales, and cognitive assessment by the MATRICS.

Missing data during follow-up will be handled using the restricted maximum likelihood method in mixed-effects linear regression analyses, allowing for the use of all data regardless of whether a participant completes the study, consistent with ITT analysis.

Clinical and demographic differences between groups will be initially evaluated at baseline using the Chi-square test for categorical variables and Student’s *t*-test for independent samples in continuous variables. These same tests will also be employed to identify potential differences between participants who complete the study and those considered to be dropouts. A participant will be considered a dropout if they miss any of the intervention protocol sessions, resulting in a loss of four sessions of intermittent theta burst stimulation (iTBS). A significance level of *p* < 0.05 will be adopted in all statistical analyses.

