Differences between the baseline, after intervention, and follow-up (T0, T1, and T2) for each measure will be tested using mixed-effects linear models. The treatment effect will be estimated through the interaction between the intervention group (intervention or sham) and the assessment time (T0, T1, and T2). Effect estimates will be presented as post-intervention mean differences, along with 95% confidence intervals, *p*-values, and Cohen’s d effect sizes (where 0.2 represents a small effect, 0.5 represents a moderate effect, and 0.8 represents a large effect). Random effects from repeated measures within each subject will be modeled according to the covariance structure that shows the lowest index based on the Akaike information criterion (AIC). The following covariates will be included in the models: the Calgary Depression Severity Scale score, as depressive symptoms may confound the assessment of negative symptoms and individuals with severe depression will be excluded from the sample; the total score of the Clinical Global Impression-Severity scale (CGI-S), since the severity of illness may influence treatment response; and the Generalized Anxiety Disorder 7-item scale (GAD-7), due to anxiety symptoms. For the various exploratory analyses conducted with the previously detailed secondary outcomes, the significance value will be corrected for multiple tests using Bonferroni criterion, with an alpha of 0.05 divided by the number of tests.

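### The Bonferroni rule for the exploratory secondary tests is valid, but Holm's step-down rule gives the same family-wise control and never rejects less (a minor efficiency point)

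*Protocol article*

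**What the plan says.** Section 2.5 (Statistical Analysis) of the protocol article opens the multiplicity rule with "For the various exploratory analyses conducted with the previously detailed secondary outcomes" and continues that "the significance value will be corrected for multiple tests using Bonferroni criterion, with an alpha of 0.05 divided by the number of tests". Every test in the family therefore faces the same threshold, 0.05/m. No stepwise procedure is mentioned, and m is not given. The same section sets a general 0.05 level for all analyses; I read the Bonferroni sentence as the specific rule for this family.

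The secondary outcomes in section 2.5 are the PANSS negative subscale, the BNSS sub-domains, HRV, two sleep scales and the MATRICS battery. Section 2.3 defines the HRV part as "calculating measures in the time domain (SDNN, RMSSD, and pNN50), in the frequency domain (VLF, LF, HF, and LF/HF ratio), and sample entropy", which is eight indices. Section 2.4 lists nine MATRICS subtests in six domains. Effects are to be reported with ordinary 95% confidence intervals.

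**The concern.** The plan has chosen to control the family-wise error over the secondary tests. For that aim, Holm needs the same assumptions as Bonferroni (none about dependence), gives the same guarantee and never rejects fewer hypotheses. Fixing the single-step rule gives up some power with no gain in error control.

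At stake is a small number of missed findings on sleep, cognition, HRV and symptom sub-domains. The Introduction says these assessments are there to help establish mechanisms. Power for each is already modest once the correction is applied.

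**Working it through.** **1. The plan's own figure.** Section 2 gives two groups "with 30 subjects per group", f = 0.38 and a two-sided 5% level, and says "The statistical power for the primary analysis with this sample size is estimated to be β = 0.82" (the value is a power, although printed as β). With two equal groups d = 2f = 0.76. The noncentrality is f²N = 0.1444 × 60 = 8.664, and the noncentral F(1, 58) power is 0.825. This agrees with 0.82.

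**2. Size of the family, per time contrast.**
- PANSS negative: 1
- BNSS sub-domains: 5 (assumed; the number is not stated)
- HRV: 8
- Sleep: 2
- Cognition: 6 domains or 9 subtests

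The total is 1 + 5 + 8 + 2 + 6 = 22, or 25 with nine subtests. Separate contrasts for T1 and T2 would enlarge it.

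**3. Power per test under Bonferroni.** The threshold is 0.05/22 = 0.00227 or 0.05/25 = 0.00200. With 30 per arm (58 df), power per truly affected outcome is 0.39 to 0.41 at d = 0.76 and 0.11 to 0.12 at d = 0.5.

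**4. The two rules compared.** Order the p-values p(1) ≤ … ≤ p(m). Holm rejects in order for as long as p(j) ≤ 0.05/(m − j + 1). With m = 22 the thresholds run 0.05/22, 0.05/21, 0.05/20, …, 0.05.
- *It keeps all Bonferroni rejections.* If a p-value is at most 0.05/m, so are all smaller ones. Every Holm threshold is at least 0.05/m, so Holm rejects it too.
- *Error control.* With m₀ true nulls, the first false rejection comes no later than step m − m₀ + 1, where the threshold is at most 0.05/m₀. Summing over m₀ nulls gives at most 0.05, whatever the dependence.
- *First rejection.* Both rules need p(1) ≤ 0.05/m, so the chance of at least one rejection is identical.

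**5. Simulation.** The settings were t-tests with 58 df, 30 per arm, and m = 22 and 25. With all nulls true, both rules gave the same family-wise error (0.043 to 0.049). With a mixture of true and false nulls, Holm's error was at most 0.049. No Bonferroni rejection was lost in any run.

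Holm's gain over Bonferroni with m = 22 and equal correlation of 0.3 to 0.6 between outcomes:

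| Outcomes that respond | Extra detections per trial, d = 0.5 | Extra detections per trial, d = 0.76 | Trials with an extra detection, d = 0.76 |
|---|---|---|---|
| 5 of 22 | 0.01–0.02 | about 0.05 | about 6% |
| 11 of 22 | 0.07–0.10 | about 0.36 | about 28% |
| 22 of 22 | 0.4–0.7 | 2.3–2.5 | about 63–72% |

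For scale, at d = 0.76 Bonferroni detects about 4.5 outcomes if half respond and about 9.0 if all do.

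**The case against.** **Nothing is invalid, and the tests are exploratory.** This stands. Bonferroni protects the error rate, section 2.5 calls these analyses exploratory, and the primary BNSS comparison is not involved. But the plan commits to family-wise control for these tests, so it is fair to ask which rule delivers it at least cost.

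**The larger gains rest on favourable assumptions.** This also stands. d = 0.76 is the planning value for the primary outcome, and nothing in the article supports it for HRV, sleep or cognition. The Discussion cites a small effect on cognition, although after a single session in healthy subjects. At d = 0.2 with all 22 outcomes responding, the gain is about 0.01 detections. In favour of the broad scenario, the Introduction does expect improvement across sleep, symptom severity and cognition.

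**Bonferroni offers matching simultaneous intervals and one fixed threshold.** This is true, and Holm has no simple equivalent intervals. The plan reports ordinary 95% intervals, however, so nothing planned would be lost.

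**A stronger reading that does not hold.** A reader might infer that the loss is especially large here because the family is large and the eight HRV indices, one of them a ratio of two others, are redundant. After k rejections Holm relaxes the threshold by m/(m − k), so for a given k a larger family means a smaller gain: with k = 5 the factor is 8/3 = 2.67 at m = 8, 22/17 = 1.29 at m = 22 and 44/39 = 1.13 at m = 44. With five true effects at d = 0.76 and correlation 0.3, the simulated gain per outcome falls in step, from about 5 points to 1.1 to 0.4. Holm also uses no information on correlation, so it does not remove the conservatism that redundant indices cause.

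**Conclusion.** The point holds as a minor efficiency improvement. For the stated aim of family-wise control at 5%, Holm is at least as good as the planned rule in every case and better in some, and it asks for no added assumption.

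The gain is negligible if few outcomes respond, small at d = 0.5 unless the response is broad, and material (about 2.3 to 2.5 more detections) only if all 22 outcomes respond at d = 0.76. It would be wrong to infer that the plan discards many detectable effects, or that its error rate is at fault.

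The sizes rest on an assumed 22 tests, five BNSS sub-domains, equal correlation of 0.3 to 0.6, and a common effect across the responding outcomes. The dominance of Holm over Bonferroni in rejections rests on none of these.

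**What to change.** In section 2.5, replace the clause that fixes Bonferroni at 0.05 divided by the number of tests with: *Holm step-down procedure at family-wise 0.05*. Apply it to the same secondary tests and report Holm-adjusted p-values. The change should be made before unblinding.

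The cost is one sentence, with no additional data or assumptions. The only thing given up is the option of simple simultaneous intervals matched to the test decisions, which the plan does not use.

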## 3. Discussion

This study aims to evaluate the effects of an accelerated iTBS protocol on negative symptoms of schizophrenia, aiming to establish an effective and feasible protocol for clinical application. To achieve this, clinical assessments will be utilized, along with their association with cognitive aspects, sleep, and heart rate variability (HRV), which will be fundamental for understanding the interaction between the clinical and biological aspects involved.

Recent studies have shown the therapeutic potential of TMS for negative symptoms in schizophrenia. A meta-analysis study that included a total of 2633 participants indicates the efficacy of this therapeutic modality, especially when the target of intervention is the left dorsolateral prefrontal cortex (DLPFC). However, there is a high risk of bias due to substantial heterogeneity among the included studies [35]. These results were corroborated by a comparative review study of non-invasive neuromodulation techniques. One justification for this could be the underlying mechanism of action of the left DLPFC on negative symptoms, as well as its relationship with other structures implicated in these symptoms, such as the midline of the cerebellum [48]. This reinforces the premise of the efficacy of repetitive TMS across distinct symptom domains rather than focusing on specific diagnoses [49]. On the other hand, a randomized, double-blind, placebo-controlled, multicenter clinical trial involving 175 patients with schizophrenia and predominantly negative symptoms did not observe the efficacy of active treatment with 15 sessions of high-frequency rTMS on the left DLPFC. One possible reason for the non-significant result was the relatively small number of sessions [50].

In this context, accelerated protocols (two or more TMS sessions in a single day) emerge as a safe and effective alternative, capable of substantially reducing the total treatment time. Theta burst stimulation (TBS), which delivers TMS pulses in bursts at gamma frequency (e.g., 50 Hz) repeated at theta frequency intervals [51], has been utilized in this type of protocol due to its short session duration [52]. This technique has increasingly been used in the treatment of psychiatric disorders [53], since its inception as a powerful means of inducing neuroplasticity [9,54]. This is evidenced by an open study by Cole et al., 2020 [13], in which patients with treatment-resistant depression achieved a remission rate of approximately 90% in just 5 days of treatment. This type of protocol may influence the adjustment of factors that directly affect treatment response, such as the number of sessions per day, total session duration, the inter-session interval, and the total number of sessions in TMS treatment [12]. The efficacy of treatment with iTBS appears to be dose-dependent, as previously observed, with a more favorable intervention effect seen in patients who received stimulation with ≥1800 pulses per day over a total of ≥20 sessions [55].

Considering studies that have utilized iTBS for negative symptoms of schizophrenia, there is still considerable uncertainty in treatment, particularly regarding variations in the type of protocol and the number of sessions, as well as the brain region to be stimulated. When comparing the efficacy of different high-frequency TMS protocols (10 Hz and 20 Hz) with iTBS in treating prominent negative symptoms, the TBS group showed significantly greater reductions in these scores [56]. A recent meta-analysis that included 12 studies with iTBS intervention in participants with prominent negative symptoms revealed a larger effect size favoring iTBS, especially in cases where the targets were aimed at the left DLPFC (compared to cerebellar targets), as well as greater effects in symptom relief for protocols with a higher total number of iTBS pulses [11]. Although a single iTBS has shown promise, accelerated protocols with longer intervals (60 min) between sessions using this technique appear to improve outcomes through additive metaplasticity, preventing homeostatic metaplasticity from stabilizing the effects of stimulation [52].

Other parameters, such as cognition, sleep, and HRV assessment, may broaden the findings of the study, contributing to an understanding of the mechanisms of improvement in the treatment and its potential relations to the nervous system. A meta-analysis of the effects of iTBS in healthy subjects suggests that a single session improved cognition with a small effect size [57]. In schizophrenia, neuromodulation on the left DLPFC by iTBS was associated with improved visuospatial working memory after 14 sessions (using a 3-back task) [58] and enhanced social cognition after 20 sessions [18]. Considering these initial findings, our hypothesis is that an accelerated protocol will impact working memory functions, specifically visuospatial working memory, measured by the Matrics span task.

Regarding sleep, the activity of the prefrontal cortex—a crucial brain area for cognition, emotion, and behavior, including sleep regulation—could be enhanced by iTBS, potentially increasing cortical activity and improving functional connectivity, which is a measure of communication between different brain areas. For instance, an improvement in sleep quality might be associated with a reduction in negative symptoms. Moreover, sleep assessment may help identify potential treatment responders, serving as a predictor of therapeutic response [59].

Furthermore, exploring the impact of neuromodulation on HRV will contribute to filling a gap in the literature regarding the link between DLPFC functioning and autonomic nervous system regulation in schizophrenia. Resting vagal activity in people with schizophrenia, measured through HF and RMSSD variables, is lower compared to healthy individuals [25] and unaffected first-degree relatives [60], as well as HRV complexity (Poincaré measures), indicating impaired physiological adaptation in recovery after stress [61].

Ma et al. observed that patients with greater insight impairment (as measured by the G12 PANSS variable) present lower HF values, poorer medication adherence, and greater working memory deficits. However, the relationship between autonomic impairments, cognitive functioning, and negative symptoms in individuals with schizophrenia remains underexplored [62]. Although research on this topic is still limited, DLPFC stimulation via rTMS has resulted in increased HRV, enhanced cardiac vagal control, and reduced arousal in autism [63] and in the modulation of the fronto-vagal network in depression [64]. In schizophrenia, no study has explored HRV modulation after iTBS, nor its association with negative symptoms and cognition and the association between HRV, negative symptoms in schizophrenia and sleep quality. HRV emerges as a measurable biomarker that, in addition to investigating the relationship between the autonomic nervous system and the clinical profiles of patients, particularly those with predominant negative symptoms, facilitates the exploration of response indicators and potential predictors of the effects of neuromodulation.

In summary, the effects of the accelerated iTBS protocol on negative symptoms have been investigated with promising perspectives; however, there is a need to establish a protocol that is both effective and feasible, particularly regarding high dosage. Although some protocols of this nature demonstrate efficacy, logistical barriers often compromise clinical application, complicating patient adherence. In this accelerated protocol, the patient will spend a short period daily (just over 3 h), which may indeed enhance feasibility. Furthermore, this project provides a platform to deepen the understanding of the effects of neuromodulation on physiology, contributing to the comprehension of the underlying mechanisms involved.

## 4. Limitations

We will not utilize functional neuronavigation as a method for targeting stimulation, which is considered the most precise technique for this type of intervention, due to practical and logistical limitations. Instead, we will employ the Beam F3 technique based on the international 10–20 system used in electroencephalography. This technique is validated for such interventions and is widely used. Regarding the blinding of the study, the applicator will not be blinded to the intervention, as the equipment requires changing the coils depending on the type of intervention (active or sham). This issue will be minimized by ensuring that the applicator does not have contact with the evaluations and assessors involved in the study.

## 5. Conclusions

This study is a randomized, double-blind, sham-controlled clinical trial comparing groups of subjects with negative symptoms of schizophrenia. It will investigate the effects of an accelerated iTBS protocol on the left DLPFC through clinical assessments, a neuropsychological battery, and heart rate variability measurements. It is expected that the results of this study will contribute to the optimization of therapeutic protocols for this disorder, particularly concerning clinical applicability.

## Figures and Tables

**Figure 1 brainsci-15-01021-f001:**
[figure not shown]
CONSORT flowchart of the recruitment process. DSM-5 (Diagnostic and Statistical Manual of Mental Disorders, Fifth Edition), BNSS (Brief Negative Symptom Scale), PANSS (Positive and Negative Syndrome Scale), HRV (hear rate variability), SCID (Structured Clinical Interview for DSM Disorders), SAS (Simpson-Angus Scale), GAD-7 (Generalized Anxiety Disorder), DLPFC (Dorsolateral Prefrontal Cortex), iTBS (Intermittent Theta-Burst Stimulation), T1 (timepoint 1), T2 (timepoint 2).

## Data Availability

Not applicable.

## Abbreviations

The following abbreviations are used in this manuscript.

iTBS	Intermittent theta burst stimulation
NS	negative symptoms
BNSS	Negative Symptom Scale
NIBS	Non-invasive brain stimulation
TMS	Transcranial Magnetic Stimulation
DLPFC	Dorsolateral prefrontal cortex
HRV	Heart rate variability
PANSS	Positive and Negative Syndrome Scale
PSQI	Pittsburgh Sleep Quality Index
ESE	Epworth Sleepiness Scale
GAD-7	Generalized Anxiety Disorder-7
MCCB	MATRICS Consensus Cognitive Battery
CDSS	Calgary Depression Severity Scale
SAS	Simpson–Angus Scale
DSM-5	Diagnostic and Statistical Manual of Mental Disorders
SCID-5	Structured Clinical Interview for DSM-5
ECG	Electrocardiogram
AIC	Akaike information criterion
CGI-S	Clinical Global Impression-Severity scale
LF	Low frequency
HF	High frequency
RMSSD	Root mean square of consecutive differences
EMG	Electromyography
